### This Study

We hypothesize that the uTECH+YMHP intervention will be considered acceptable, appropriate, and feasible by most participants. Furthermore, we hypothesize that participants receiving the combined uTECH+YMHP intervention will show greater and more sustained reductions in substance use and sexual risk behaviors compared to those receiving the YMHP intervention alone. Specifically, we anticipate that the integration of ML-informed SMS text messages will enhance the efficacy of YMHP counseling methods by providing personalized, timely, and contextually relevant support, ultimately leading to improved health outcomes in this sample of SGM young adults.

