### The uTECH Intervention

Participants randomized to receive the uTECH intervention (uTECH+YMHP) will receive SMS text messages that use the Information-Motivation-Behavior Skills (IMB) model [51] to improve substance use harm reduction and promote safer sex practices. The IMB model was developed to use information, motivation, and behavioral skills to promote HIV-related behavior change, positing that when groups at risk for HIV are well informed, motivated to act on their knowledge, and have the necessary behavioral skills to seek out and initiate change, they will successfully overcome obstacles to make behavior change. The IMB model is effective in enhancing protective health behaviors such as adherence to interventions or reduction of risk behaviors with people living with HIV or AIDS [52-54] and people who use substances [55-57].

Staff will follow the IMB framework to generate content for the SMS text messages, a process that will be informed by an extensive review of public health messaging, scientific literature, and validated survey instruments tailored for specific subgroups that will be recruited for this study. The groups include people who inject drugs, people who do not inject drugs, people who are on PrEP, people who are not on PrEP, transgender and nonbinary people who are on PrEP, and transgender and nonbinary people who are not on PrEP. Each participant will be assigned to 1 of the above subgroups based on their answers in their baseline interview. The SMS text messages will be sent to participants using Twilio (version 8.0.0; Twilio Inc) [58], a web-based communications service that can be programmed to send and receive SMS text messages. Approximately 2 SMS text messages will be scheduled per week, so that each participant will receive 100 text messages over the course of 12 months.

To obtain feedback, participants will be asked to respond to each SMS text message. Participants will be compensated US $1 per SMS text message to which they reply. Each SMS text message also includes an opt-out option to comply with cell carrier antispam policies. The feedback from participants will also be used to enhance the ML algorithm in preparation for fully automated SMS text message generation and assignment (Table 1).

**Table 1 table1:** Text message content examples from the uTECH intervention using the Information-Motivation-Behavior Skills (IMB) model.

	PrEP^a^ initiation	PrEP adherence	Sexual risk reduction	Substance use harm reduction

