### Discharge From the Study

Participants will be discharged from the study after they complete their 12-month assessment and offboarding. At their final interview, Android-using participants will receive instructions on how to uninstall the eWellness app from their phone. The study team will also discontinue sending automated SMS text messages to uTECH+YMHP participants.

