### Planned Analytic Approach

Primary outcomes for the study include the acceptability, appropriateness, and feasibility of each intervention condition. In addition, we will examine behavioral health outcomes (sexual risk and protective behaviors and substance use) in both intervention conditions. Tests of fixed effects for estimates of time-specific differences will be performed using appropriate contrasts. Trend changes and their significance will be analyzed, driven by variance components (random effects). We will use growth curve modeling [75] to examine the effects of treatment on outcomes. Growth curve factors also account for the covariation of follow-up observations within participants. Data from 3-, 6-, 9-, and 12-month follow-up assessments will be modeled using latent growth factors using R statistical software [76] (version 4.4.0; R Foundation for Statistical Computing). Because the first nonbaseline time point in the latent growth curve will be the 3-month follow-up, significant differences in the intercept factor would indicate significant postintervention effects. Significant differences in slope factors would indicate that the groups follow different trajectories. When this is noted, potential group differences at each follow-up assessment will be evaluated by varying the location of the referent time point.

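### The growth model reads a 3-month intercept difference as postintervention, although uTECH runs to month 12 and the trial was sized on a time-averaged difference

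*Protocol article*

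**What the plan says.** The Planned Analytic Approach states that "Data from 3-, 6-, 9-, and 12-month follow-up assessments will be modeled using latent growth factors". The first modelled wave is the 3-month follow-up, and on that basis "significant differences in the intercept factor would indicate significant postintervention effects". For the slope, "Significant differences in slope factors would indicate that the groups follow different trajectories". The next sentence makes re-centring conditional: "When this is noted, potential group differences at each follow-up assessment will be evaluated by varying the location of the referent time point". The same section also announces, without a condition, that "Tests of fixed effects for estimates of time-specific differences will be performed using appropriate contrasts". Mediation and Moderation then defines a significant group difference by the treatment coefficient on the intercept or slope factor.

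On timing, YMHP Sessions puts the fourth and last session in month 2, in both arms. For the uTECH arm, "each participant will receive 100 text messages over the course of 12 months". Discharge From the Study follows the 12-month assessment, and it is there that "The study team will also discontinue sending automated SMS text messages to uTECH+YMHP participants".

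Sample Size Calculation and Power Analysis uses acceptability and a time-averaged difference over five measurements (baseline and four follow-ups). It targets 9 points at autocorrelation 0.1, or 11 points at 0.5, with 80% power. The hypothesis in This Study is that the combined arm "will show greater and more sustained reductions in substance use and sexual risk behaviors" compared with YMHP alone.

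**The concern.** There are two mismatches.

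1. **Label.** A 3-month difference comes after YMHP, but the arms do not differ in YMHP. They differ in uTECH, which still has nine months to run. Calling the 3-month difference postintervention describes the wrong component. A reader of the results could take an early on-treatment difference for an effect of the completed intervention.

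2. **Target.** The trial was sized on the average difference over time, but the growth model's stated criteria are the difference at the first wave and the difference in slope. An intercept at the edge of the time range is estimated less precisely than the average. If the benefit is constant, the slopes do not differ, and within this model detection rests on that edge intercept alone. The power statement therefore does not describe the test that the model is set up to make.

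**Working it through.** **Timing.** Messages sent by month 3: 100 × 3/12 = 25. YMHP ended in month 2. The last assessment, at month 12, comes before the messages are stopped, so no assessment follows the end of uTECH.

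**Inputs.** From the sample size section: N = 330; 95% retention, so 330 × 0.95 = 313, about 156 per arm; reference proportion 85%; AR(1) correlation ρ = 0.1 or 0.5; differences of 9 or 11 points; 80% power; α = .05. Assumed: two-sided test, linear growth, AR(1) as the total covariance, binary acceptability as in the sizing. The protocol does not say whether the difference is upward or downward from 85% (its closing sentence speaks of an increase), so both are shown.

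**The plan's own figure.** The variance of a mean of m AR(1) measures is the single-measure variance times f = (sum of all entries of the m × m correlation matrix)/m². For m = 5, f = 0.235 (ρ = 0.1) and 0.445 (ρ = 0.5). Power is

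Φ( d / √( f [p₁(1−p₁) + p₂(1−p₂)] / n ) − 1.96 ).

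At n = 156 per arm, the difference detectable with 80% power is 5.1 points up or 5.9 down at ρ = 0.1, and 6.8 up or 8.3 down at ρ = 0.5. The stated 9 and 11 are not reproduced. Using four follow-ups, a change from baseline, baseline adjustment, a smaller α or smaller arms did not give both figures with two arms of this size.

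**Precision of the intercept against the average.** For a linear model at waves 0, 1, 2, 3 with design matrix X = [1, t] and correlation R, the generalised least squares variance factor of the first-wave intercept is the top-left entry of (X′R⁻¹X)⁻¹.

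| | ρ = 0.1 | ρ = 0.5 |
|---|---|---|
| 3-month intercept | 0.758 | 0.935 |
| Mean of four follow-ups | 0.290 | 0.516 |
| SE ratio | √(0.758/0.290) = 1.62 | √(0.935/0.516) = 1.35 |

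Placing the intercept of the same fitted line at 7.5 months, the mean of 3, 6, 9 and 12, gives 0.289 and 0.500. That is essentially the precision of the average.

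**Power relative to a stated 80%.** If the four-wave average has exactly 80% power, its standardised effect is 1.96 + 0.842 = 2.802. The intercept then has Φ(2.802/1.62 − 1.96) = 41% at ρ = 0.1 and Φ(2.802/1.35 − 1.96) = 55% at ρ = 0.5. Against the five-measure average the figures are 34% and 49%. The penalty shrinks as correlation rises: at ρ = 0.9 the intercept would have about 75%.

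**Power on the protocol's inputs, constant effect, n = 156 per arm.** Example, 85% v 94% at ρ = 0.1: SE = √(0.758 × (0.1275 + 0.0564)/156) = 0.0299; 0.09/0.0299 − 1.96 = 1.05; power 85%.

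| | Intercept | Average (4 to 5 measures) |
|---|---|---|
| 9 points up, ρ = 0.1 | 85% | 99.8% to >99.9% |
| 9 points down, ρ = 0.1 | 64% | 96% to 99% |
| 11 points up, ρ = 0.5 | 94% | 99.7% to 99.9% |
| 11 points down, ρ = 0.5 | 71% | 92% to 95% |

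**Growing effect.** If the effect rises linearly from zero at baseline and averages 9 (11) points over the follow-ups, the month-3 effect is 9 × 3/7.5 = 3.6 (11 × 3/7.5 = 4.4) points. Intercept power, upward, is about 19% (23%). In that case the slope test carries signal as well.

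**The case against.** The strongest reply is that the intercept is one of several named tests and is not ranked first. Slopes and time-specific contrasts are also planned, and naming the primary contrast is often left to an analysis plan that is not shown. Centring time is only a reparameterisation of the same fitted model. The month-12 contrast sits at the other edge and has the same variance as the month-3 intercept. The behavioural hypotheses are secondary. All of this is fair, and it lowers the severity. What remains is that the article itself fixes an intercept location and a reading that its own delivery schedule contradicts, and that it makes intercept or slope coefficients the criterion for a significant difference while sizing on something else.

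A reader might infer three stronger conclusions, which the documents do not support:

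- **That the trial has about half its planned power.** The 41% to 55% holds only if the average has exactly 80%. The protocol's inputs give the average more than that, and they give the intercept 64% to 94% for a constant effect.
- **That a 12-month benefit may never be tested.** The conditional sentence governs only re-centring of the growth model. The sentence on time-specific contrasts carries no condition.
- **That the durability hypothesis cannot be tested.** It is stated relative to YMHP alone, and YMHP ends in month 2. Whether continued messaging holds gains better than none can be examined with the 3- to 12-month data. Persistence after messaging stops cannot.

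**Conclusion.** The point holds as a problem of labelling and alignment. A 3-month difference between arms is an on-treatment difference with about a quarter of uTECH delivered. The growth model's criteria do not include the time-averaged difference used for sizing. For a constant benefit, relying on the 3-month intercept costs a factor of 1.35 to 1.62 in standard error. That ratio does not depend on whether the protocol's 9% and 11% reproduce, but it does rest on linear growth and AR(1) errors with ρ between 0.1 and 0.5, and it is smaller at higher correlation. How much power is lost in absolute terms depends on which sizing figures are believed, so it should be given as the two ranges above and not as a single headline number.

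**What to change.** 1. Code time so that zero lies at 7.5 months. The group effect on the intercept is then the time-averaged difference over the four follow-ups. Name it the primary contrast and restate power for it, noting that the current 9% and 11% do not follow from the stated inputs and that the sizing counted baseline as a fifth measurement.
2. Report the 12-month contrast whether or not the slopes differ, as a supporting result, since it is no more precise than the 3-month one.
3. Replace the postintervention label with wording such as: at 3 months, during uTECH.
4. Word any conclusion on sustained or durable change as a comparison with YMHP alone while messaging continues.

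The cost is recoded time scores, a new power calculation and text edits; no new data are needed. The price is giving up any suggestion of persistence after uTECH ends. The Results section says analysis is under way, so the change should be dated and recorded before arm comparisons are examined. If they have already been seen, it should be reported as a later change.

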### Missing Data

We will impute any missing values, based on the characteristics of the data and the assumptions of the final analyses, such as using multiple imputation if data are missing at random [77]. While analyses of treatment effects are questions of differences after the intervention, baseline data will be used to inform and supplement analyses. For example, baseline data will be used to evaluate whether randomization successfully equated groups on demographic variables and other covariates of theoretical significance. We will use baseline data to evaluate correlates of differential attrition, if observed. If randomization fails or attrition produces group differences, models will use baseline data to control for covariates that are nonorthogonal with treatment condition. We will use growth mixture modeling techniques, including latent class growth curve modeling, to evaluate any meaningful patterns in outcome variable responses across time. We will examine whether treatment condition is associated with outcome response pattern.

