### Target Population

This study aims to recruit 330 participants. Half (n=165, 50%) of the participants will be randomized to receive uTECH+YMHP (condition 1), and the remaining half (n=165, 50%) will be randomly assigned to receive YMHP only (condition 2).

To be eligible for the study, participants must be aged 18 to 29 years, identify as SGM, have had anal or oral sex with a man (defined by the participant’s interpretation) in the past 3 months, have used substances (such as alcohol, marijuana, amyl nitrate [poppers], methamphetamines, heroin, cocaine, and ecstasy) in the past 3 months, have had sex while using substances in the past 3 months, have a negative or unknown HIV status, and have used a dating app to meet sexual or substance use partners in the past 3 months. Participants must also own a smartphone, reside in the United States, be willing to participate in a 12-month study, and be able to provide informed consent. Participants that use an Android smartphone as their primary device must consent to install the eWellness app on their phone to remotely collect keystroke and geolocation data throughout the duration of the study. Participants who use an iOS (Apple Inc) smartphone must provide the study team with at least 1 set of data from both their primary dating app and their most-used social media account every 6 months. Failing to meet all the stated criteria would disqualify individuals from enrollment in the study. Exclusion criteria were conceived to build upon existing literature for HIV prevention in SGM populations while also expanding gender criteria to be inclusive of transgender and gender nonbinary individuals who have sex with men. Our study population aims to capture the identities of young adult users of queer-centered dating apps and websites such as Grindr, Scruff (Perry Street Software, Inc), and Sniffies (Sniffies, LLC) who may be at heightened risk of HIV and STI transmission [17-19], particularly in the context of substance use [5-9].

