### Automated SMS Text Messages (uTECH+YMHP Participants)

Participants assigned to the uTECH+YMHP intervention will receive approximately 2 SMS text messages per week that provide resources promoting sexual wellness and substance use harm reduction. Participants are assigned to specific subgroups based on their answers to the baseline interview to ensure that SMS text messages are tailored. Participants are compensated US $1 per SMS text message to which they respond, and this amount is disbursed at 4 time points corresponding to their 3-, 6-, 9-, and 12-month assessments.

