### Expected Timeline

Development of the initial version of eWellness was completed in October 2020, and enrollment for the trial started soon after. The eWellness app continued to undergo refinement and development until phase 2 began in November 2021. Enrollment will continue until the target sample size is reached, with 12 months of study engagement per participant. We expect to complete data collection 12 months after the last participant has been enrolled in the study, that is, by June 2024, and plan the dissemination of results subsequently.

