### Statistical Analyses

Statistical methods, models, and procedures will be selected according to the research hypotheses being tested and the types of measures involved. We will set α<.05 as the level for statistical significance but will use appropriate corrections for multiple comparisons (eg, Bonferroni and Hochberg correction [73]) to ensure that the actual overall effective type 1 error remains at an α=.05 level for the tests to be conducted. The frequency and patterns of missing data will be carefully evaluated. To avoid potential bias resulting from missing data, imputation (eg, hot deck or multiple imputation [74]) will be conducted, and statistical significance tests and modeling will be conducted with and without the imputed values. The findings from these analyses will be compared, and any differences will be evaluated. Potential nonlinear relationships between continuous predictors (eg, participants’ age) and outcomes (eg, acceptability, appropriateness, and feasibility of uTECH and YMHP) will be evaluated through spline functions (eg, cubic spline).

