### Sample Size Calculation and Power Analysis

For the power calculation, we used 1 primary outcome, acceptability. We used a balanced repeated measures design [84] with pretreatment baseline measurements. Using a logistic regression generalized linear mixed model [85], we allowed an individual’s 5 measurements (baseline and 3-, 6-, 9-, and 12-month) for acceptability to be correlated via an autoregressive-1 structure. With an initial sample size of 330 (to account for 95% retention), an autocorrelation of 0.1, and a baseline effectiveness of 85%, we aimed to detect a minimum time-averaged difference of 9% in acceptability between any 2 conditions, maintaining 80% power and an a priori α level of .05. This calculation was based on pairwise comparisons between uTECH+YMHP versus YMHP-only conditions. If the autocorrelation [86] between measures within the same individual was as high as 0.5, the sample size was adjusted to detect a minimum difference of 11% between the 2 conditions. A 9% to 11% difference between the 2 conditions is considered statistically significant, given the existing evidence supporting YMHP and the relative cost-effectiveness and ease of delivery of the uTECH intervention. The ability to demonstrate a small increase in the acceptability of uTECH over YMHP will support the widespread implementation of uTECH in future efficacy trials.

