## Results

This study was funded in August 2019. Between August 2019 and June 2024, we have enrolled 424 participants on a rolling basis. Approximately 71% (301/424) of the study participants have completed 12 months of participation. Data collection concluded in June 2024. Data analysis is currently under way, and expected results will be published in the fall of 2025.

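### With 71% completing 12 months against 95% planned, the named handling of missing ratings and its stated checks cannot detect dropout related to dislike of the intervention

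*Protocol article*

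**What the plan says.** Under Missing Data, the protocol article states "We will impute any missing values, based on the characteristics of the data and the assumptions of the final analyses". It gives multiple imputation as the example for data missing at random and names nothing for data that are not. Under Statistical Analyses, it lists hot deck and multiple imputation as examples. It then says that "statistical significance tests and modeling will be conducted with and without the imputed values", with any differences between the two evaluated.

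The article plans three further checks. It will examine the frequency and patterns of missing data. It will look for baseline correlates of differential attrition. It will control for baseline covariates if attrition makes the groups differ.

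On expected loss, Sample Size Calculation and Power Analysis reads: "With an initial sample size of 330 (to account for 95% retention), an autocorrelation of 0.1, and a baseline effectiveness of 85" percent. On actual loss, Results reports: "Approximately 71% (301/424) of the study participants have completed 12 months of participation", with data collection closed in June 2024.

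The primary outcomes are acceptability, appropriateness and feasibility, rated by survey at 3, 6, 9 and 12 months (Primary Outcomes).

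**The concern.** When the outcome is how acceptable people find a programme, whether they answer the survey may depend on the answer they would have given. Someone who comes to dislike the counselling or the texts has a reason to stop responding. Imputation under missing at random gives that person ratings like those of comparable people who stayed.

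At the planned 5% loss this would hardly matter. At 29% it can move an arm's acceptability by an amount worth reporting. The planned checks would not show it, because each of them works within missing at random.

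A second, separate problem is that hot deck appears alongside multiple imputation as an equal option. A single hot deck analysed as if the filled-in values had been observed understates the standard error, and the understatement grows with the missing fraction.

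**Working it through.** **Inputs.** 424 enrolled and 301 completing 12 months (Results). N = 330, 95% retention, 85% baseline figure and a 9-point target difference, or 11 points at the higher autocorrelation (Sample Size Calculation and Power Analysis). 1:1 allocation (Target Population). The acceptability of the missing is not given anywhere, so a range is assumed. Not completing 12 months is taken as having no month-12 rating; this is a close inference and is not stated.

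**1. Loss, planned and actual.**
- Planned: 330 × 0.95 = 313.5 evaluable, 5% lost.
- Actual: 301/424 = 0.710, which agrees with the stated 71%. Lost: 424 − 301 = 123, and 123/424 = 0.290, about 5.8 times the plan.

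**2. Overstatement of month-12 acceptability in one arm.** Bias = missing fraction × (rate among observed − rate among missing), with the observed at 85%.

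| Missing would be at (assumption) | True rate, 29.0% missing | Overstated by | Overstated by at 5% missing |
|---|---|---|---|
| 75% | 82.1% | 2.9 points | 0.5 |
| 65% | 79.2% | 5.8 points | 1.0 |
| 50% | 74.9% | 10.2 points | 1.8 |

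As bounds, if none of the missing found it acceptable the true rate is 0.710 × 85% = 60.3%. If all did, it is 60.3% + 29.0% = 89.4% before rounding.

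**3. Difference between arms.** Bias = m₁g₁ − m₂g₂, where m is the missing fraction and g the rating gap in each arm.
- With equal m and g this is zero.
- No loss by arm is reported. For illustration, with 25% v 33% missing (assumption), the shift is 0.08 × 35 = 2.8 points if the missing are at 50%, and 0.08 × 85 = 6.8 points if they are at 0%. The direction depends on which arm loses more.
- For the bias to equal the 9-point target through one arm alone, that arm would need a gap of 0.09/0.290 = 31 points and the other arm none.

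**4. Single hot deck treated as real data, one visit.** True variance / naive variance = n/r + (n − r)/n, with n in total and r observed.
- At 29%: 424/301 + 123/424 = 1.409 + 0.290 = 1.699. The standard error ratio is 1.30, and type I error is 2(1 − Φ(1.96/1.303)) = 0.133. A simulation of 40,000 trials with 212 per arm at 85% gave 0.136.
- At 5%: 330/313.5 + 16.5/330 = 1.103. The ratio is 1.05 and type I error 0.062 (simulated 0.062).

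**5. What the planned checks can see.** The analysis without imputation rests on missing at random or on something stronger, and the imputed analysis rests on missing at random. Agreement between them is therefore no evidence against informative dropout. The attrition correlates and the covariate control use baseline variables, so they cannot pick up dislike that forms after the programme begins.

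**The case against.** Much can fairly be said for the plan.

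- **Scope.** This is a journal article, and an unseen analysis plan may hold more. The wording is conditional and gives examples. That stands as a caution. But the article does state which methods it has in mind and how they will be checked, and that check does not address the main risk for this outcome.
- **More than one check.** It would be wrong to say that the only check is imputed against unimputed results. The pattern evaluation, attrition correlates and covariate control are real. They still do not test for data missing not at random.
- **Numbers.** 424 were enrolled, and 301 completers is close to the planned 313.5. The issue is therefore bias and error rate more than lost power. Nor is there reason to rewrite the 95% figure, which was a prior assumption.
- **Estimand.** The analysis uses growth curves and the sample size a time-averaged difference, while 29% is a 12-month figure. Loss at 3, 6 and 9 months is not given, and early ratings from later dropouts carry information. The effect on those estimates is probably smaller than at month 12.
- **Truncation.** Expected Timeline says "We expect to complete data collection 12 months after the last participant has been enrolled in the study, that is, by June 2024", while Results dates enrolment as running to June 2024. Some of the 123 may have been cut off by the calendar, which has no evident link to dislike. The share is unknown.

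A reader might also infer several stronger points that the documents do not support:

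- **Acceptability is biased upward.** No figure shows that non-completers rate lower.
- **The bias exceeds the 9-point target.** A shift in one arm's level is not a shift in the difference between arms.
- **Text payments give only one arm a reason to stay.** The article says "this amount is disbursed at 4 time points corresponding to their 3-, 6-, 9-, and 12-month assessments", which gives the timing and does not make payment depend on completing the survey.
- **Text ratings would be imputed in the YMHP-only arm.** Table 2 lists the two sets of ratings separately, and an item that does not apply is not missing.

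**Conclusion.** The concern holds as a risk that the stated plan cannot detect; it does not demonstrate bias. Loss at 12 months is 29% against 5% planned. At that level, plausible departures from missing at random would overstate an arm's month-12 acceptability by about 3 to 10 points, given 85% among the observed and 75% down to 50% among the missing (assumptions). The between-arm difference is affected only if loss or the gap differs by arm, and could move either way.

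The hypothesis that most participants find the combined intervention acceptable is not overturned by these figures: even with every missing rating counted against it, 85% among the observed leaves 60%. What is at stake is the reported level and the comparison between arms.

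The error-rate point, about 13% in place of 5% at month 12, applies only to a single hot deck without variance correction. It disappears with proper multiple imputation.

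**What to change.** 1. Remove hot deck as an option. Use multiple imputation with a model that includes the earlier ratings as well as arm and baseline covariates.
2. Add delta-adjusted multiple imputation, with delta varied separately by arm, and report the tipping point at which the conclusion changes.
3. Add a sensitivity analysis that counts withdrawal or non-response as not acceptable. Exclude administrative truncation from that rule, since counting it would bias the rate downward.
4. Report the 123 non-completers by arm, by last visit and by reason (dropout or truncation).

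No new data collection is needed. Because the article says analysis is already under way, the additions should be dated and described as specified at that stage. The cost is a little more analysis and possibly a less favourable acceptability figure.
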